### Outcome measures

#### Primary outcome measures

The primary outcomes measures for the PREMOM II study will be: (1) prenatal follow-up data, including the numbers of prenatal consultations, ultrasounds, cardiotocograms, hospitalizations to a prenatal ward, and duration of hospitalization; (2) delivery data, including duration of labor, complications, mode of delivery, and date of delivery; (3) neonatal data, including gestational age at delivery, date and hour of delivery, APGAR, birth weight, length, complications, NICU hospitalization, and duration of hospitalization; (4) RM data, including duration of participation, number of contacts with the pregnant women regarding vital signs, number of contacts with the responsible obstetrician, numbers of prenatal consultations and hospitalizations due to RM data, and information about the interventions; and (5) compliance rates in the midwife-assisted RM and PSM groups.

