### Sample size calculations

Sample size calculations were performed by Censtat (Hasselt University, [name], [name]) to detect clinically meaningful differences between the midwife-assisted RM group and the CG in women with GHD, for two key factors (1) gestational age for neonates born before 34 weeks and (2) admission to the prenatal ward for neonates born after 34 weeks, based on previous work.
Gestational age for neonates born before 34 weeks: a difference of ≥10 days between the midwife-assisted RM group and the CG was observed in our pilot studies, and was used as a clinically relevant difference for the power calculation. Priority was given to this sample size calculation because each 1-day increase in gestational age at birth has a significant impact on the neonate’s short- and long-term outcomesAdmission to the prenatal ward of neonates born after 34 weeks: a proportional difference of 20% between the midwife-assisted RM group and the CG was considered clinically relevant. This outcome was expected to be most frequent in the PSM group, followed by the CG group, and less likely in the RM group.

The sample size calculations are based on summary statistics derived from our pilot study. A power of 80% and a significance level of 1.67% was used. A within-center variance of 6 (for gestational age) and a random intercept standard deviation of 0.0875 (for prenatal ward admission) was assumed. To obtain 80% power, we estimated that ≥168 GHD pregnancies with delivery before the gestational age of 34 weeks and ≥ 360 GHD pregnancies admitted to the prenatal ward after 34 weeks would need to be included in the study. At each center, the women will be equally divided into the three study groups.

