Based on the numbers from Studiecentrum voor Perinatale Epidemiologie (Brussels, Belgium), these 168 births before 34 weeks account for 6.6% of a total of 2545 GHD deliveries. Furthermore, GHD pregnancies represent 4.6% of the total number of pregnancies (55,335) per year [1]. As observed in prior studies, 68% of women with GHD require interventions for their GHD, we estimate a ratio of 100 to 68 pregnant women (or 1.47 to 1) will be needed for the RM group to treat one patient with GHD. As such, 6.76% (4.6% × 1.47) of these women are at risk of developing GHD, meaning 3741 women will need to be enrolled in our study. Taking into account a dropout rate of 4.83% (based on our previous studies), we will need to enroll a total of 3922 women and screen 57,998 women.

For the second sample size calculation (admission to a prenatal ward after 34 weeks), we estimated that > 360 women delivering at a gestational age later than 34 weeks will need to be enrolled across the four prenatal wards. Based on prior studies, ≥42% of women with GHD will be admitted to a prenatal ward. Therefore, out of 5931 deliveries after 34 weeks (6107 eligible women – 176 [168 + dropout rate of 4.83%] who will deliver before 34 weeks), approximately 2491 mothers will be hospitalized. As such, the sample size needed to assess this outcome is expected to be satisfied by the sample size required to show a difference in gestational age in deliveries before 34 weeks.

The primary statistical analysis will entail comparisons among the three study groups using the two-sided Fisher’s exact test at a significance level of 0.05. Adjustment for baseline variables will be performed if necessary, and interaction analyses will be performed using multivariable logistic regression analyses. The median, 95% confidence intervals, quartiles, means, and standard deviation will be calculated as appropriate.

The statistician will be blinded to the study groups.

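### The named primary test, Fisher's exact test at 0.05, does not fit the endpoint that sets the sample size (mean gestational age, sized at 1.67%) or the many primary outcomes that are counts, durations or measurements

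*Protocol article*

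**What the plan says.** All places are in the protocol article.

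- **Sizing, priority endpoint** (Sample size calculations). The first key factor is gestational age in births before 34 weeks, compared between the midwife-assisted remote monitoring (RM) group and the control group (CG): "a difference of ≥10 days between the midwife-assisted RM group and the CG was observed in our pilot studies". It takes precedence over the second factor: "Priority was given to this sample size calculation because each 1-day increase in gestational age at birth has a significant impact".
- **Sizing, second endpoint** (same section). Prenatal ward admission for births after 34 weeks, with a 20% difference in proportions between the same two arms.
- **Sizing assumptions** (same section). "A power of 80% and a significance level of 1.67% was used", and "A within-center variance of 6 (for gestational age) and a random intercept standard deviation of 0.0875 (for prenatal ward admission) was assumed". The stated needs are 168 early births and 360 pregnancies after 34 weeks, divided equally over three arms.
- **Primary analysis** (end of the same section). "The primary statistical analysis will entail comparisons among the three study groups using the two-sided" Fisher's exact test, at the 0.05 level. Then: "Adjustment for baseline variables will be performed if necessary", with logistic regression for interactions. Means, medians and standard deviations appear only as summaries. No test for means or counts is named.
- **Outcomes** (Primary outcome measures). The prenatal set is listed as "including the numbers of prenatal consultations, ultrasounds, cardiotocograms, hospitalizations to a prenatal ward, and duration of hospitalization". The other sets add duration of labour, gestational age, Apgar score, birth weight and length. Mode of delivery, complications and NICU admission are the plainly categorical ones.

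**The concern.** Fisher's exact test works on a contingency table. Gestational age, visit counts, lengths of stay and birth weight can enter it only after being cut into categories. The article gives no cut-points, so they would have to be chosen later, possibly with data in view. Cutting a continuous outcome also discards information, and the endpoint affected is the one that sets the enrolment target.

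Three further mismatches sit in the same section. The sizing uses 1.67%, the analysis 0.05. The sizing assumes centre structure, while the named test has no centre term. Baseline adjustment is conditional on need without a criterion, so the choice between an adjusted and an unadjusted answer could follow the results.

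**Working it through.** **Inputs.** From Sample size calculations: difference of at least 10 days, within-centre variance 6, alpha 1.67% (0.05/3), power 80%, 168 and 360 women in three equal arms (56 and 120 per arm), and at least 42% of women with gestational hypertensive disorder admitted. Assumptions made here: variance in weeks squared (no unit is given), normal data, two-sided sizing, the 20% read as percentage points, and 42% taken as the CG admission rate.

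**Step 1: reproduce 168.** For two means, n per arm = 2σ²(z₁₋α/₂ + z₀.₈)²/δ². With α = 0.05/3 the z-values are 2.394 and 0.842, so (3.236)² ≈ 10.47 and 2 × 6 × 10.47 ≈ 125.6.

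- δ = 1.5 weeks (10.5 days): 125.6/2.25 = 55.8, so 56 per arm and **168** in total, exactly as stated.
- δ = 10 days (1.429 weeks): 125.6/2.041 = 61.6, so 62 per arm and 186 in total.

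The stated figure is therefore consistent with a comparison of means, with δ slightly above 10 days.

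**Step 2: power at 56 per arm, means versus a split.** A split midway between the arm means gives proportions Φ(±δ/(2√6)): 62.0% versus 38.0% for 1.5 weeks, and 61.5% versus 38.5% for 10 days. Fisher power was enumerated exactly, by summing the product of the two binomial probabilities over all tables with p ≤ α.

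| Pairwise RM vs CG | 10 days | 1.5 weeks |
|---|---|---|
| t-test, 1.67% | 74% | 79% |
| Fisher on split, 1.67% | 45% | 50% |
| t-test, 0.05 | 86% | 89% |
| Fisher on split, 0.05 | 61% | 65% |

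Three other cuts were tried: at the control mean, and one SD above and below it. All gave less power, 19–47% at 1.67%. With the continuity-corrected formula, regaining 80% on the midpoint split would take 98–107 per arm (294–321 in total) at 1.67%, or 75–82 per arm (225–246) at 0.05, against 168 planned.

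**Step 3: three-group reading.** If the analysis is one overall test of three groups at 0.05, simulation (6,000 runs, self-monitoring group set equal to CG, midpoint split) gives 71–75%.

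**Step 4: ward admission.** For 42% versus 22%, the two-proportion formula gives 113 per arm (339 in total), or 123 (369) with continuity correction, close to the stated 360. Exact Fisher power at 120 per arm is:

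| Rates | 1.67% | 0.05 |
|---|---|---|
| 42% vs 22% | 80% | 90% |
| 52% vs 32% | 73% | 86% |
| 60% vs 40% | 72% | 84% |

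**Step 5: alpha.** Three independent tests at 0.05 would have a family-wise error of 1 − 0.95³ ≈ 14%, and less when the comparisons share arms. The sizing level, 0.05/3, fits a Bonferroni split over three comparisons.

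**The case against.** A reader might infer that the planned analysis cannot deliver the planned power at all. The document does not support that. Ward admission is binary, Fisher's test suits it, and its power is roughly kept. For gestational age, the article plans no median or midpoint split, so the loss depends on a cut that is not stated. Births before 34 weeks are also truncated at 34 weeks, so normality is only approximate. Since the article attaches 0.05 to Fisher's test, the 45–50% at 1.67% is not the plan as literally written. The three-group reading at 0.05 (71–75%) comes near the 74–79% of a comparison of means at 1.67%. All this stands, and it limits the figures to illustrations. It does not remove the loss at equal alpha.

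Other strong readings also fail:

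- *The test is an overall test that misses RM versus CG.* The wording on comparisons among groups is plural, and 1.67% is 0.05/3, so pairwise tests are a fair reading.
- *Leaving out centre invalidates the comparison.* Arms are balanced within each centre. A simulation of admission with centre SD 0.0875 (five equal centres, 42% vs 22%) gave 79–80% power for Fisher and 83–84% for a centre-stratified test at 1.67%, a gap of a few points.
- *Ignoring the medication subgroup biases the arm comparison.* It is randomised 1:1 within every arm (Subgroup randomization), so unadjusted arm comparisons remain valid.

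It can also be said that a separate analysis plan may supply models and covariates. That answers the missing covariate list, which is no fault of an article. It does not answer a primary test that is named and does not fit the priority endpoint.

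**Conclusion.** The point holds in limited form. The article fixes one primary test that cannot be applied to its priority endpoint, or to many other primary outcomes, without categorising them, and it sets an alpha different from the one used for sizing. On a midpoint split the loss for gestational age at equal alpha is about 29 percentage points at 1.67% and about 25 at 0.05. This rests on normality, variance in weeks squared and the assumed cut; the other cuts tried were worse. For binary ward admission no material loss is shown at 42% versus 22%, and the missing centre term there costs little. The 1.67% versus 0.05 conflict and the open-ended adjustment clause need settling in the same edit. The mismatch on gestational age alone is enough to require correction before any analysis by arm.

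**What to change.** Replace the single-test sentence with a primary analysis by outcome type:

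- gestational age and other continuous outcomes: linear (mixed) model with a centre term;
- visit counts and durations: a count model or a rank-based test;
- binary outcomes such as ward and NICU admission: Fisher's test, or logistic regression with a centre term.

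State RM versus CG as the primary contrast, tested at the 1.67% used for sizing. Replace the conditional adjustment clause with covariates fixed in advance. Which covariates is the team's choice; the Fetal Medicine Foundation risk, calculated for every woman before randomisation, is one candidate.

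Cost: a wording change in the protocol or analysis plan and slightly more analysis work. No new data are needed.

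### The named primary test, Fisher's exact, does not match the continuous endpoint that set the sample size or the many count and duration primary outcomes

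*Protocol article*

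**What the plan says.** All of this is in the protocol article.

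- **Primary analysis** (Sample size calculations, near the end): "The primary statistical analysis will entail comparisons among the three study groups using the two-sided Fisher’s exact test at a significance level of 0.05". No outcome type is attached to the sentence.
- **Other methods** (same place): baseline adjustment is foreseen if needed, with no model clearly tied to it, and "interaction analyses will be performed using multivariable logistic regression analyses". Medians, quartiles, means, standard deviations and 95% confidence intervals are to be calculated as appropriate. No test or model for a continuous or count outcome is named.
- **Sizing** (same section): gestational age among births before 34 weeks has priority. The effect is described as follows: "a difference of ≥10 days between the midwife-assisted RM group and the CG was observed in our pilot studies". The variability is given as "A within-center variance of 6 (for gestational age) and a random intercept standard deviation of 0.0875 (for prenatal ward admission) was assumed", and the error rates as "A power of 80% and a significance level of 1.67% was used". The result is "we estimated that ≥168 GHD pregnancies with delivery before the gestational age of 34 weeks", and at each centre "the women will be equally divided into the three study groups".
- **Primary outcomes** (Primary outcome measures): the prenatal set is described as "including the numbers of prenatal consultations, ultrasounds, cardiotocograms, hospitalizations to a prenatal ward, and duration of hospitalization". The other sets add duration of labour, gestational age, Apgar score, birth weight, length, duration of hospitalisation and numbers of contacts. They also contain categorical items, such as mode of delivery, complications and NICU admission.

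**The concern.** Fisher's exact test works on a table of counts in categories. It does not compare mean gestational age, mean numbers of consultations or lengths of stay. Logistic regression is likewise a model for categorical outcomes.

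As written, the primary analysis therefore fits some primary outcomes and the second sizing endpoint (prenatal ward admission), but not the endpoint that drove the enrolment target of 3922. Two routes are open, and both are awkward:

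- The team follows the sentence and cuts gestational age, visit counts and durations into categories. Power is lost, and the cut-points become choices that the article has not fixed.
- The team uses a suitable method instead. The analysis then departs from the published primary analysis.

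The trial's first hypothesis, in the Discussion, concerns numbers of prenatal consultations and unplanned visits, so the question reaches beyond gestational age.

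**Working it through.** **Inputs from the article.** Difference of at least 10 days (10/7 = 1.43 weeks); within-centre variance 6; alpha 1.67%; power 80%; 168 births in three equal groups, so 168/3 = 56 per group; analysis alpha 0.05.

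**Assumptions, not in the article.** Variance in weeks squared, so SD = √6 = 2.449 weeks; a normally distributed outcome; any cut-point.

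**1. Reproduce the 168.** For two means, n per group = 2σ²(z₁₋α/₂ + z₁₋β)²/δ². With two-sided alpha 0.0167, z = 2.393; for 80% power, z = 0.842; the squared sum is 10.464.

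- δ = 1.5 weeks: 2 × 6 × 10.464 / 2.25 = 55.8, so 56 per group and 3 × 56 = **168**, an exact match.
- δ = 10 days exactly: 12 × 10.464 / 2.041 = 61.5, so 62 per group and 186.

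The figure is thus a comparison of means, apparently with the difference taken as 1.5 weeks (10.5 days).

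**2. Power of the analysis that was sized.** Two-sample t-test, 56 per group, δ = 1.5 weeks (non-central t): 79% at 1.67% and 89% at 0.05. The normal formula gives 80% and 90%.

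**3. Power if gestational age is dichotomised and Fisher's test is used.** The most favourable cut for a pairwise comparison is midway between the two means. The proportions above it are Φ(0.75/2.449) = 0.620 and 1 − 0.620 = 0.380. Power is the summed probability of all pairs of binomial results with a two-sided Fisher p-value at or below alpha.

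| Remote monitoring v control, 56 per group | alpha 0.0167 | alpha 0.05 |
|---|---|---|
| t-test, 1.5 weeks | 79% | 89% |
| Fisher, midpoint cut, 1.5 weeks (62% v 38%) | 50% | 65% |
| Fisher, midpoint cut, 10 days (61% v 39%) | 45% | 61% |
| Fisher, cut 2 weeks below the control mean, 1.5 weeks (21% v 8% below) | 26% | 41% |

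The last row only illustrates how much the choice of cut matters. At 1.67% with the best cut and 1.5 weeks, Fisher power is 79.8% at 96 per group and 80.6% at 97. So 80% needs 3 × 97 = 291 births, against 168.

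**4. One overall comparison of three groups at 0.05.** This is closer to the stated sentence. Take the same midpoint cut and let self-monitoring equal control, as the Discussion expects for outcomes. The proportions are 0.620, 0.380 and 0.380, with mean p̄ = 0.460. In the chi-square approximation, λ = 56 × Σ(pᵢ − p̄)² / [p̄(1 − p̄)] = 8.70 on 2 df, which gives 76% power. For a 10-day shift, λ = 7.91 and power is 71%. A three-group F-test on the uncut outcome would have 92% and 90%. If self-monitoring instead lay midway between the other two, the 3×2 comparison would have 62% and 58%.

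**5. Counts treated as categories.** The extension of Fisher's test to larger tables can be run on each distinct value as a category, but it ignores order and size. If all values are distinct, every possible table is equally likely and the p-value is 1.

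**The case against.** The strongest reply is that this is a condensed article. Tests for each outcome commonly sit in a full protocol or analysis plan that is not shown, and one sentence naming a test for proportions may be shorthand for the categorical outcomes, which include the second sizing endpoint. The text also promises 95% confidence intervals, which are inferential, and leaves the adjustment model open. This stands in part: it is not shown that the trial will use only categorical methods. It does not remove the point, because the article does more than leave a method out. It names one primary test, without restriction, that conflicts with its own priority endpoint.

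Two stronger readings are tempting. A reader might infer that most primary outcomes have no usable test at all. That goes too far: counts can be cut or treated as categories, unplanned visits can be analysed as any versus none, and several outcomes are truly categorical.

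A reader might also infer that the trial's 80% power is already lost. The article does not support that either. It nowhere says that gestational age will be dichotomised and gives no cut-point. The power figures describe what would follow if the sentence were applied literally. They also assume a unit and a normal shape for births that are in fact truncated at 34 weeks. The pairwise figures at 1.67% are lower than those for the stated three-group comparison at 0.05, where the shortfall is modest if self-monitoring equals control.

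**Conclusion.** The point holds as a mismatch between the stated primary test and the outcomes it is meant to serve. That mismatch follows from the text alone and needs no assumption.

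Its size is conditional. With variance in weeks squared, a normal outcome and 56 births per group, dichotomising gestational age at the best cut leaves pairwise power of about 50% at 1.67% or 65% at 0.05 for a 1.5-week shift. An overall three-group comparison at 0.05 has about 71–76% for shifts from 10 days to 1.5 weeks with self-monitoring equal to control. Every case examined is below 80%, and the looser alpha of 0.05 does not make good the loss. Because the conflict concerns the primary analysis of the endpoint that set enrolment, it should be corrected before any comparative analysis.

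**What to change.** Amend the primary analysis statement, and the analysis plan to match:

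- Restrict Fisher's exact test to categorical outcomes, for example ward admission, NICU admission and mode of delivery.
- Analyse gestational age as a continuous outcome in a linear model that includes centre. Report the difference in days with its confidence interval, at the significance level used for sizing (1.67%).
- Name a count model for numbers of visits and procedures, and a method suited to skewed data for durations. Which particular model is a matter for the analysis plan.
- For interaction tests on non-binary outcomes, use the model that matches the outcome, not logistic regression.

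The cost is wording only: no further data or participants. The change should be dated and made before unblinded data are examined.

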### Randomization

Figures 2 and 3 show the randomization process, trial flow and timeline table (according to SPIRIT). Randomization will be performed between 11 and 14 weeks of gestation, after the first trimester ultrasound examination. Using the Castor EDC web-based system, the women will be randomized to one of the three study groups at a 1:1:1 ratio by the study midwives, who also perform the inclusion in the PREMOM II study and the further RM follow-up (Figs. 2 and 3).

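### The trial is sized at 1.67% but its primary analysis is stated at 0.05 with no link between the two, and no lead outcome is named among five primary domains

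*Protocol article*

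**What the plan says.** Three statements in the protocol article bear on this point.

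- **Sizing.** Under Sample size calculations the numbers were chosen "to detect clinically meaningful differences between the midwife-assisted RM group and the CG in women with GHD, for two key factors": gestational age in births before 34 weeks, and prenatal ward admission after 34 weeks. For both, "A power of 80% and a significance level of 1.67% was used". The first of the two calculations was given priority.
- **Analysis.** At the end of the same section: "The primary statistical analysis will entail comparisons among the three study groups using the two-sided Fisher"'s "exact test at a significance level of 0.05". Nothing connects this 0.05 to the 1.67%, and the text does not say whether the comparison is overall or pairwise.
- **Primary outcomes.** Primary outcome measures lists five domains (prenatal follow-up, delivery, neonatal, RM process and compliance), each with its own items and none marked as the lead. The last is "5) compliance rates in the midwife-assisted RM and PSM groups". Gestational age at delivery and prenatal ward hospitalization appear as two entries among many, without the 34-week restriction used in the sizing.

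**The concern.** A level of 0.05/3 in the sizing signals an intention to correct for three pairwise comparisons, and the trial was made larger to pay for it. The analysis sentence then gives the uncorrected figure. A reader cannot tell whether the correction survives into the analysis. If it does not, the error rate that the sizing was meant to protect is lost.

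The long primary list is a second gap, which a change of alpha alone would not close. The two outcomes that determine the size are not designated as the primary tests, and no order or split of alpha connects the listed measures. The Discussion says that the results are meant to help persuade caregivers, hospital administrators and government, so a confirmatory claim needs a defined error rate.

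**Working it through.** **Inputs.** Three arms ("the women will be randomized to one of the three study groups at a 1:1:1 ratio"); sizing alpha 1.67%; power 80%; analysis alpha 0.05; "A within-center variance of 6 (for gestational age"), unit not stated and assumed here to be weeks squared; and "a difference of ≥10 days between the midwife-assisted RM group and the CG was observed in our pilot studies".

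**1. Where 1.67% comes from.** Three arms give three pairs, and 0.05/3 = 0.01667. The article does not label the figure, so Bonferroni is an inference, but the match is exact to the digits given.

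**2. Which alpha produced the 168.** Per arm, n = 2σ²(z₁₋α/₂ + z₀.₈₀)²/δ², with σ² = 6 and three equal arms.

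| Two-sided alpha | δ = 1.5 weeks (assumed) | δ = 10 days (1.43 weeks) |
|---|---|---|
| 0.0167 | 56 per arm, 168 | 62 per arm, 186 |
| 0.05 | 42 per arm, 126 | 47 per arm, 141 |

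The stated 168 is reproduced at two-sided 0.0167 if the difference is taken as 1.5 weeks. Neither difference gives 168 at 0.05. So 1.67% was used in the sizing. The 186 at exactly 10 days is a separate matter.

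**3. Error within one outcome.** This depends on what 0.05 means.

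- *Each pairwise test at 0.05:* 12.2%, from simulating three equal arms so that the shared arms are allowed for. It would be 1 − 0.95³ = 14.3% if the tests were independent, and the upper bound is 3 × 0.05 = 15%.
- *Each pairwise test at 0.0167:* 4.4% by the same simulation; upper bound 5%.
- *0.05 as an overall test or family level:* held at 5%.

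**4. Error over the two sized outcomes, if independent.**

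- Pairwise at 0.05: 1 − (1 − 0.122)² = 22.9%.
- Pairwise at 0.0167: 1 − (1 − 0.0442)² = 8.6%.
- One overall test each at 0.05: 1 − 0.95² = 9.8%.

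All three exceed 5%, so the gap across outcomes does not depend on how the 0.05 is read.

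**5. Length of the primary list.** The domains hold 5 + 4 + 8 + 6 + 1 = 24 items (23 to 25, depending on how compound items are split). The first three domains, 5 + 4 + 8 = 17, are defined in all arms. With 17 independent tests at 0.05 the chance of at least one false positive would be 1 − 0.95¹⁷ = 58%. With three pairwise tests per item it would be 1 − (1 − 0.122)¹⁷ = 89%. These two figures are illustrative only, for the reasons given in the objection.

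**The case against.** The analysis sentence does not say that three pairwise tests are each run at 0.05. It can be read as one three-group test at 0.05, or as 0.05 for the family with 1.67% as the share of each pair. With three groups, an overall test at 0.05 followed by pairwise tests at 0.05 is itself a closed procedure that holds the error within an outcome. This objection stands: 12% and 23% are conditional figures.

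It also stands that the 17 items are not 17 separate hypotheses. Delivery date appears in two domains, gestational age, birth weight and length move together, and many items are counts, durations or continuous values that Fisher's exact test does not fit. The 58% and 89% overstate the real rate and should not lead the argument.

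A reader might infer that any nominal p below 0.05 would count as a positive primary result. The article gives no success rule, so the text does not support that. A reader might also infer that the three-group test will be run on domains that do not exist in the CG. The article itself limits compliance to the RM and PSM arms and does not say that RM-process data will be tested across three groups, so this is a minor point.

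Finally, an analysis plan not shown here may set a testing order, and the sizing text does give priority to gestational age. But that priority attaches to a calculation, not to a test. The two alpha levels and the undifferentiated primary list are in the article's own text, so the conflict does not rest on anything left to another document.

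**Conclusion.** The point holds in this form: the article gives two significance levels, 1.67% and 0.05, and leaves their relation open. If 0.05 applies to each pairwise test, the familywise error is about 12% for one outcome and about 23% for the two sized outcomes, the latter assuming independence. If it is an overall or family level, the error within one outcome is held, so it would be too strong to say that the per-outcome error is uncontrolled.

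What holds on every reading is that error across the primary outcomes is not controlled. About 24 items in five domains are primary, none leads, and the two sized outcomes are not named as the primary tests. Even the mildest reading, one overall test at 0.05 on each sized outcome, gives 9.8% if they are independent. Correlation lowers such figures, but no provision in the text brings the overall rate to 5%.

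**What to change.** - **Alpha.** In the primary analysis sentence, state that RM vs CG, RM vs PSM and PSM vs CG are each tested at two-sided 0.0167, matching the sizing. Alternatively, describe an explicit closed procedure at 0.05 overall.
- **Lead outcome.** Name gestational age in births before 34 weeks, which the sizing already put first, as the lead primary outcome. Analyse it with a method for continuous data instead of Fisher's exact test.
- **Order.** Test prenatal ward admission only if the lead succeeds.
- **Other measures.** Make the remaining items secondary, and report RM-process and compliance data descriptively.

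The cost is wording in the protocol and analysis plan and a registry update. Fewer outcomes can be called primary, and the second sized outcome can be claimed only if the lead succeeds. The alpha assumed in the sizing is unchanged, so the change needs no extra women.

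Splitting alpha over three comparisons and both sized outcomes (0.05/6 = 0.0083) would cost more. On the 1.5-week assumption it needs 65 per arm (195 in all), and power at 56 per arm falls to about 73%. The article reports recruitment as incomplete at submission, and the change should be made before any comparison by arm is seen.
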